#### Quantitative – Patient medical record review

Data from patient medical records will be tabulated for an exploratory descriptive comparison of the two groups. The primary purpose will be to provide additional context to qualitative data, particularly the VSR interview and case study analysis (see below). Between-group comparisons will be explored as above.

#### Within-case analysis

A subsample of 10 patients who demonstrate the most positive intentions and/or behaviours to reduce CVD risk following the Health Check will be selected for case study analysis, drawing on all data for each patient. The aim is to further explore apparent mechanisms by which the risk calculators may lead to changes in patient or practitioner behaviour (Obj. 5). A coding framework for deductive analysis of qualitative data based on potential mechanisms of eliciting health-protective intentions/behaviours will be generated from findings in recorded Health Checks, and VSR patient and practitioner interviews, and applied to qualitative data in each case study (Health Check, and patient and practitioner VSR interviews). The quantitative data on Health Check content and subsequent actions would be used to provide a basic profile for each patient to aid interpretation.

### Sample size

A priori determination of sample sizes for qualitative research is a point of contention [45, 46]. For the present study, it was necessary to estimate requirements for the patient VSR interviews and use this to inform the total number of recorded Health Checks required per practice. As summarised in Table 3, 48 VSR patient interviews (24 per group, 4 per practice) will allow patient sampling stratified by gender, age and CVD risk, and provide a sample size that compares favourably with studies using VSR or audio-recordings of primary care consultations (ranging from *n* = 9–44 [42, 43]). These 48 recorded Health Checks will be selected (with stratification) from 144 (72 per group, 12 per practice) that are subject to deductive qualitative analysis; i.e., 12 per practice was deemed sufficient to allow stratified sampling of four patients per practice. To obtain the 144 recorded Health Checks that are suitable for qualitative analysis, we will aim to record 240 (120 per group, 20 per practice). This oversampling will serve two purposes. First, it will allow for exclusions due to non-attendance, technical issues and Health Checks that contain little or no discussion of CVD risk. Second, with 120 consultations per group, using a between subjects t-test with a two-tailed probability and alpha of .05, we will have statistical power of at least .8 to detect a small to medium effect (Cohen’s d) = 0.37. It will also mean that the effect sizes derived from the study will have good levels of precision for estimating the effect sizes in future studies and so provide more accurate power analysis for such studies.

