## Methods/design

### Design and setting

This qualitative study, which includes a quantitative process evaluation, will be undertaken in 12 general practices in the West Midlands that already deliver NHS Health Checks. Six practice pairs, approximately matched on practice size and deprivation, will be randomly assigned to one of two groups: QRISK®2 (usual practice) - practitioners continue to use QRISK®2 to communicate CVD risk during Health Checks; JBS3 (intervention) - practitioners use the JBS3 CVD risk calculator following brief training about the platform, but no training will be provided about risk communication. Participating practices will video-record their NHS Health Checks using the allocated CVD risk calculator over until 20 useable consultations are recorded. As summarised in Fig. 2 and detailed below, data collection will comprise: (1) Video-recording NHS Health Check consultations; (2) Post-consultation video-stimulated recall (VSR) interviews with patients and practitioners within 2 weeks, using excerpts from recorded health checks to facilitate recall and reflection; (3) Patient medical record reviews 12-weeks post-Health Check to determine subsequent action (e.g., GP appointment, lifestyle referral, statin prescription).

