### Sample

#### General practices

General practices that meet the following criteria will be recruited: a) deliver NHS Health Checks; b) already use the QRISK®2 percentage risk score in Health Checks; currently (or willing to) deliver Health Checks in specific clinics to facilitate data collection; c) are signed up to the ‘incentive scheme’ implemented by the Clinical Research Network (CRN) to ensure the GP practice is ‘research ready’; d) are willing to participate.

General practices will be stratified using data on practice list size and deprivation level of the practice location [40] to provide a proxy measure of typical socio-economic status of the practice population (Table 1).

**Table 1 Tab1:** Stratified sampling of six practices per group based on deprivation and list size

	Deprivation	
Practice list size	Most deprived 50%	Least deprived 50%
Small-Medium (< 8000)	2 QRISK®2; 2 JBS3	2 QRISK®2; 2 JBS3
Large (≥8000)	1 QRISK®2; 1 JBS3	1 QRISK®2; 1 JBS3

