#### Quantitative - content of health check consultations

The content of the recorded consultations will be characterised using a coding framework that involves second-by-second coding of Health Check content. The framework comprises 36 items grouped in to six categories (patient-practitioner communication, general Health Check processes, risk dialogue, CVD risk factors, lifestyle interventions, medical interventions). The resulting data will provide aggregate indicators for each consultation to allow between-group comparisons (e.g., proportion of Health Check considered practitioner- or patient-dominated; proportion of time discussing risk; proportion of time discussing intervention/changes; number of times the practitioner manipulated the risk score to illustrate amenability of risk to change).

The development of the coding process and guide was iterative. Four “mock” Health Checks were undertaken by practitioners and PPI volunteers. These were video-recorded and two researchers (LC; NE) coded the consultations by consensus to reach consistency in approach. A third researcher (VR) then coded all four consultations independently. Intraclass Correlation Coefficients (ICCs) were calculated and demonstrated excellent inter-rater reliability (ICCs ranged from .968 to .995). The resulting framework will be refined during a training/checking phase with study data, whereby an additional four recorded Health Checks (2% of total) will again be independently coded by two researchers and inter-rater agreement assessed. Once finalised, two researchers (LC; VR) will code the remaining Health Check recordings independently (118 each). For every 20 coded consultations (8% of total), two would be subject to independent verification (independent coding and calculation of ICCs). This will mitigate the risk of coder drift throughout the study and provide independent verification of 10% of consultations overall.

A between subjects t-test or non-parametric equivalent will be used for between-group comparisons of key outcomes for Health Check content (e.g., proportion of time spent discussing CVD risk). To explore possible cohort effects within the data, ICCs will be calculated (i.e., to examine possible clustering within practices). Multi-level modelling is not appropriate; the study is designed to allow for novel qualitative enquiry and is not powered for multi-level statistical analysis.

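### The stated power of at least .8 for d = 0.37 and the promise of good precision hold only for 240 independent consultations, but 12 practices are randomised

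*Protocol article*

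**What the plan says.** Under Design and setting, the protocol article makes the practice the unit of allocation: "Six practice pairs, approximately matched on practice size and deprivation, will be randomly assigned to one of two groups". Table 1, under General practices, is titled "Stratified sampling of six practices per group based on deprivation and list size". The Practitioners section expects usually one or two practitioners per practice to deliver the checks.

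The Sample size section sets the target: "we will aim to record 240 (120 per group, 20 per practice". It gives two reasons for recording more than the 144 consultations needed for qualitative analysis. The second is statistical: "using a between subjects t-test with a two-tailed probability and alpha of .05, we will have statistical power of at least .8". The effect meant is a Cohen's d of 0.37, which the section classes as between small and medium. It then says that "the effect sizes derived from the study will have good levels of precision for estimating the effect sizes in future studies". Neither sentence mentions an intracluster correlation (ICC), a design effect or the number of practices.

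The section on quantitative analysis of Health Check content plans a patient-level t-test, or a non-parametric equivalent, for the between-group comparison. It plans to calculate ICCs to look for clustering within practices. It rejects multi-level modelling, partly because the study "is not powered for multi-level statistical analysis".

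**The concern.** When whole practices are randomised, consultations from the same practice share whatever is common to that practice. That sharing is plausible here. The outcomes are largely practitioner behaviour, such as the share of time spent on risk or how often the risk score is manipulated, and one or two people usually produce all 20 recordings in a practice. The information about the group difference then comes from six practices per group rather than 120 separate patients. A power figure and a precision statement based on 120 independent patients per group are both too favourable.

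Three things are at stake. First, the study may be less able to detect d = 0.37 than stated. Second, the planned unadjusted test would not keep the alpha of .05 on which the power statement rests, so false positives become the main danger. Third, the protocol offers its effect sizes as inputs to later power calculations. If their uncertainty is understated, a later study could be mis-sized.

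**Working it through.** **Inputs from the protocol article.** Two-sided alpha 0.05; d = 0.37 (standardised, SD = 1); 120 consultations per group; 20 per practice (Sample size). Six practices per group (Table 1).

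**Input not in the document.** The between-practice ICC for the outcome. I assume 0.02, 0.05, 0.10 and 0.20, with 0 as the limiting case.

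**Step 1: the plan's own figure.** With independent observations, SE(d) = √(2/120) = 0.129 and the noncentrality is 0.37/0.129 = 2.87. On 238 df the noncentral t gives power 0.814. The normal approximation gives 0.818, and 115 per group would suffice for 80%. The stated power of at least .8 is therefore reproduced. The 95% half-width is 1.96 × 0.129 = 0.25.

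**Step 2: a practice-level comparison.**
- Design effect: DE = 1 + (20 − 1) × ICC.
- Effective n per group: 120/DE.
- SE(d) = √(2 × DE/120).
- Degrees of freedom: 12 − 2 = 10, with t(0.975, 10) = 2.228.
- Power: noncentral t on 10 df with noncentrality 0.37/SE.
- Half-width: 2.228 × SE.

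Example at ICC 0.05: DE = 1 + 19 × 0.05 = 1.95; effective n = 120/1.95 = 62; SE = √(2 × 1.95/120) = 0.180; noncentrality = 0.37/0.180 = 2.05; power 0.46; half-width 2.228 × 0.180 = 0.40.

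| Assumed ICC | DE | Effective n per group | Power at d = 0.37 | d detectable at 80% | 95% half-width |
|---|---|---|---|---|---|
| 0 | 1.00 | 120 | 0.73 | 0.40 | 0.29 |
| 0.02 | 1.38 | 87 | 0.60 | 0.47 | 0.34 |
| 0.05 | 1.95 | 62 | 0.46 | 0.56 | 0.40 |
| 0.10 | 2.90 | 41 | 0.33 | 0.68 | 0.49 |
| 0.20 | 4.80 | 25 | 0.22 | 0.88 | 0.63 |

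**Step 3: how far this depends on the 10 df.** With the normal approximation and no penalty for degrees of freedom, power at ICC 0.02 to 0.20 is 0.68, 0.54, 0.39 and 0.26. On that basis power falls below 0.80 once the ICC exceeds about 0.0025. With 10 df it is below 0.80 even at ICC 0.

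**Step 4: the test actually planned.** An unadjusted t-test uses an SE that is too small by a factor √DE. Its true type I error is about 2 × [1 − Φ(1.96/√DE)]. A simulation of 10,000 trials, each with six practices of 20 per group, checks this and gives the rejection rate at d = 0.37.

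| Assumed ICC | Type I error, formula | Type I error, simulated | Rejection rate at d = 0.37, simulated |
|---|---|---|---|
| 0.02 | 0.095 | 0.094 | 0.78 |
| 0.05 | 0.160 | 0.160 | 0.74 |
| 0.10 | 0.250 | 0.254 | 0.71 |
| 0.20 | 0.371 | 0.379 | 0.67 |

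The rejection rates in the last column look close to the stated power, but they are bought with false positives well above 5%.

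**Step 5: pair matching.** A paired practice-level analysis has 6 − 1 = 5 df. If matching removed none of the between-practice variance, power at d = 0.37 would be 0.50, 0.38, 0.28 and 0.19 at the four ICCs. Matching that works would raise these figures, but the article gives nothing from which to judge by how much.

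**The case against.** The strongest reply is that this is a qualitative study. All its objectives are exploratory or aim at recommendations, the sample size was built up from the 48 patient interviews, and statistical power is only the second of two reasons for recording 240 consultations. This stands, and it limits the consequence. It does not make the unqualified power and precision sentences right.

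Second, the arithmetic is correct for the test named. This also stands. The fault is an unstated independence assumption, not a miscalculation.

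Third, the analysis section discloses possible clustering and plans to calculate ICCs, so clustering was not overlooked. True, but calculating ICCs afterwards changes neither the test nor the stated power, and nothing in the article ties that disclosure back to the Sample size section.

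Fourth, the powers on 10 df belong to a practice-level test that the protocol does not plan. This is fair, and it is why the type I error of the planned test must be shown beside them and why the analysis has to change together with the wording.

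A reader might infer more than the text supports in two places. One is that the two sections formally contradict each other. They do not: one gives power for a patient-level t-test, the other speaks of multi-level analysis. They are in tension, because power that is lost once the randomised unit is respected should not be stated without qualification. The other is that a null result will be taken to exclude a small-to-medium effect. The article does not say so, and specifies no confidence intervals for the between-group differences.

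**Conclusion.** The power and precision statements are wrong as written and should be corrected. They hold for 240 independent observations and not for 12 randomised practices of 20. For a valid practice-level comparison, 80% power is not reached at d = 0.37 for any ICC from 0 upwards on 10 df. Over assumed ICCs of 0.02 to 0.20 the detectable effect is 0.47 to 0.88, not 0.37, and the half-width is about 1.3 to 2.5 times the independence value (0.34/0.25 to 0.63/0.25). At ICC 0.05 or above, an observed d of 0.37 would have an interval that includes zero.

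The direction is firm. The size depends on ICCs that the article does not give, on equal practices of 20, and on no gain from pair matching. Since the comparison is a secondary process evaluation, a reader should not infer that the study as a whole is undermined: the qualitative work and the recruitment targets do not depend on this figure.

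**What to change.** No extra recruitment is needed. Three linked changes:

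1. **Sample size, power sentence.** Either drop the power claim or restate it over the full assumed range. For example: *With 12 practices of 20 consultations, a practice-level comparison on 10 df has power of about 0.60, 0.46, 0.33 and 0.22 for d = 0.37 if the practice ICC is 0.02, 0.05, 0.10 or 0.20. The effect detectable with 80% power is then about 0.47, 0.56, 0.68 or 0.88, and the 95% CI half-width 0.34, 0.40, 0.49 or 0.63. The ICCs are assumptions. Pair matching may recover some precision, but a paired analysis has 5 df.*
2. **Sample size, precision sentence.** Replace it with a statement that the study will supply SDs and practice ICCs, with confidence intervals, for planning future studies.
3. **Quantitative analysis of Health Check content.** Make the between-group comparison one of practice-level summaries, or use another small-sample method that respects clustering. Without this change, the restated power would describe a test that is not run.

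The cost is wording and a simple change of test. The stated power and precision become less favourable.

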## Discussion

This innovative study is, to our knowledge, the first to examine current risk communication practice in NHS Health Check (using QRISK®2), the potential of using the JBS3 lifetime risk calculator, and to apply novel video-recording methodological approaches in this context. The multi-faceted methodological approach has many advantages. First, video-recordings will provide an objective and ‘real-time’ record for quantitative and qualitative analysis of Health Checks. Second, video-recorded Health Checks will allow analysis of both verbal and non-verbal communication, providing a comprehensive account, with the sensitivity to capture subtle details [47]. Capturing nonverbal behaviour can convey additional emotional information that is important in the study of practitioner-patient relationships [48]. Third, VSR interviews will enhance participant recall of thoughts, perceptions and emotions during the consultation, and allow a considered reflection on their related intentions and actions [31].

The outcomes will have important implications. The national NHS Health Check programme, which remains one of only three mandatory functions included in the 2012 Health and Social Care Act and has political backing as evidenced by inclusion in *Living Well for Longer: A call to action to reduce avoidable premature mortality* [49]. New insight from our data will inform recommendations for which tool should be endorsed for Health Checks and how practitioners should make best use of them. However, in a period of growing budgetary pressure, this work has value regardless of the future of NHS Health Check as the need to effectively communicate CVD risk and prompt positive behaviour change to protect against future disease will remain a key component of primary care.

## Abbreviations

CVD: Cardiovascular disease
JBS3: Joint British Societies lifetime CVD risk calculator
NHS: National Health Service
PMT: Protection Motivation Theory
PPG: Patient Participation Group
PPI: Patient and Public Involvement
QRISK®2: Calculator to estimate the risk of having a heart attack or stroke over the 10-years
VSR: Video-stimulated recall
